## Abstract

**Background:**

Little attention has been paid to quality improvement (QI) capacity within smaller primary care practices which comprise nearly half of all primary care settings. Strategies for external support to build such capacity include practice facilitation (PF), shared learning opportunities, and educational outreach. Although PF has proven effectiveness, little is known about the comparative effectiveness of combining these strategies. Here, we describe the protocol of the “Healthy Hearts Northwest” (H2N) study, a randomized trial designed to address these questions while improving risk factors for cardiovascular disease.

**Methods/design:**

The targeted enrollment is 250 smaller primary care practices across Washington, Oregon, and Idaho. The study is utilizing a two-by-two factorial design to assess four different combinations of practice support: PF alone, PF with educational outreach, PF with shared learning opportunities, or PF with both. A mixed methods approach is being used for evaluation and will include data from (1) baseline and follow-up practice and staff surveys; (2) baseline and quarterly clinical performance measurement from each practice on four cardiovascular risk factors: appropriate aspirin use, blood pressure control, lipid management and smoking cessation support; and (3) a quality improvement capacity assessment (QICA) survey used by external practice facilitators to guide improvement efforts.

**Discussion:**

Results from this study will inform future large-scale practice improvement initiatives by providing comparisons of promising external practice support strategies and advance our understanding of how to build QI capacity in primary care.

**Trial registration:**

ClinicalTrials.gov, NCT02839382

## Background

Cardiovascular disease (CVD) is a leading cause of avoidable morbidity and mortality in the Unites States of America (USA) [1]. The US Department of Health and Human Services launched the “Million Hearts” initiative in 2011 to prevent 1 million heart attacks and strokes by 2017 [2]. Within the primary care setting, the initiative focuses improvement on four CVD risk factors, the “ABCS”—aspirin use in high risk patients, blood pressure control, cholesterol management, and smoking cessation counseling. In 2015, the Agency for Healthcare Research and Quality (AHRQ) launched the EvidenceNOW initiative to both support improvement of these CVD risk factors among patients within smaller primary care practices across the USA and to advance the science of building quality improvement (QI) capacity within primary care [3].

Although primary care is the foundation of health care delivery in the USA, little attention has been paid to the QI capacity of smaller primary care practices which comprise nearly half of all primary care settings [4]. These smaller practices often lack the staffing and resources to invest in the infrastructure and training that provide essential elements of QI capacity [5, 6]. Even when practices have resources and are committed to QI in principle, they often struggle with developing and implementing concrete strategies for making improvement [7]. The potential impact of building QI capacity is illustrated by the finding that twice as many deaths could be prevented by optimized ABCS risk factor control within primary care compared to optimizing acute cardiovascular care in the hospital setting [8].

Three specific external practice support strategies stand out as promising approaches to build QI capacity in primary care: practice facilitation (PF), shared learning opportunities, and educational outreach [7]. PF is delivered by a facilitator, usually external to the practice setting, who enables those who work within a practice to implement a change in care delivery [9]. It is a guided interactional process that has great potential and demonstrated ability to support uptake and application of scientific knowledge to improve clinical and managerial decision-making [10]. There is substantial evidence for the effectiveness of PF to support improvement in primary care settings [11, 12]. Shared learning opportunities, such as the learning collaborative approach pioneered by the Institute for Healthcare Improvement, can motivate change [13]. Educational outreach, often called academic detailing, involves a trained outside expert delivering one or more educational messages to a healthcare professional or the clinical team. It is generally considered a promising method of modifying health professional behavior, with a 5.6 % average improvement in guideline concordant behavior from one large systematic review [14].

Although PF alone has proven effectiveness to support improvement, little is known about the benefit of supplementing this strategy with shared learning, educational outreach, or both. This paper outlines the protocol of the “Healthy Hearts Northwest” (H2N) study, a randomized trial to build QI capacity in smaller primary care practices. The primary aim of the study is to compare the effectiveness of adding shared learning opportunities, educational outreach, or both to PF for building QI capacity within smaller primary care practices, with a focus on CVD risk factor control. Our primary hypothesis is that the improvement in the ABCS clinical performance measures will be greater among practices assigned to enhanced practice support arms of the study compared to practice facilitation alone, that practice capacity for QI will mediate this relationship, and that external organizational support and external climate for QI will moderate the observed relationship between intervention arm and change in ABCS outcomes. Our secondary hypothesis is that compared to national control practices not participating in the study, CVD clinical performance measures will improve across all practices enrolled in H2N and this improvement will vary across the different combinations of practice support.

## Methods

### Study setting and recruitment

The study is taking place from May of 2015 to April of 2018 in smaller primary care practices across three states: Washington, Oregon, and Idaho. H2N is a collaborative partnership between the MacColl Center for Healthcare Innovation at the Group Health Research Institute, Qualis Health in Washington and Idaho, the Oregon Rural Practice Research Network (ORPRN) based at the Oregon Health Sciences University, and the University of Washington’s Institute of Translational Health Sciences. Qualis Health is recruiting practices and providing PF support in Washington and Idaho. ORPRN is recruiting practices and providing PF support in Oregon. The recruitment goal is 250 practices: 120 in Washington, 100 in Oregon, and 30 in Idaho. To be eligible, practices must have 10 full-time or fewer providers in a single location and meet stage 1 electronic health record (EHR) meaningful use criteria. Our rationale for these priority criteria is to focus efforts on smaller practices with the greatest need for externally provided QI expertise and have some capability to produce clinical performance measure reports at the start of the study, given the relatively short 36 months of funding.

### Study design

A two-by-two factorial design is being used to compare the effectiveness of adding shared learning opportunities and educational outreach to PF. (Fig. 1) The four factors (intervention arms) are (1) PF alone, (2) PF and shared learning, (3) PF and educational outreach, and (4) PF combined with both shared learning and educational outreach. In addition, a set of control data for the ABCS clinical performance measures will be obtained from a randomly selected national sample of primary care practices not participating in the study. This control data will consist of the four ABCS clinical performance measures over the same historical time period and reporting intervals as the practices enrolled in the H2N study. Control practices will be matched on practice size (clinician FTE), QI measure reporting capabilities, and rural/urban location. This data will be provided by the DARTNet Institute [15].

**Fig. 1 Fig1:**
[figure not shown]
Factorial study design

### Practice support interventions

PF support is provided to all sites upon enrollment in the study for 15 months as a unifying approach. Two enhanced practice support interventions, shared learning through site visits and educational outreach on CVD risk calculator use, are being offered to those practices randomized to receive them over a period of 4 months approximately 3–9 months after the start of the PF support. A description of each type of external practice support follows.

### Practice facilitation and support

A geographic cluster of 10–20 practices are assigned to each practice facilitator. Each practice is receiving 15 months of support with a minimum of five face-to-face visits from the facilitator, with a monthly phone call in-between the face-to-face visits. Additional phone or video calls, emails, and text messaging are being provided as needed. A practice self-assessment tool (see measures below) is used by the facilitator in the first face-to-face visit to help the practice team achieve consensus on their current status for each of eight change concepts that build on prior practice transformation work in small primary care practices [16]. These change concepts provide direction to small practices in their efforts to transform into true learning and improvement organizations and comprise activities in the eight areas as described in Table 1. More than a decade of work by members of our team supports these concepts as foundational to build practice capacity to learn and improve [17, 18].

**Table 1 Tab1:** Quality improvement change concepts and key activities

Change concept	Description of practice activities
Embed clinical evidence on ABCS into daily work to guide care for patients	▪ Review the evidence supporting the ABCS for primary and secondary prevention of cardiovascular risk ▪ Review treatment guidelines for ABCS measures ▪ Educate staff on clinical guidelines ▪ Select patient education materials for primary and secondary prevention
Utilize reliable, robust data to understand and improve ABCS measures	▪ Develop process to pull data from EMR ▪ Review data for accuracy and build confidence in data ▪ Develop process to support accurate data entry/collection ▪ Use data to identify gaps between the evidence-based guidelines and current care for all patients on panel ▪ Create population-based reports and visual data dashboards
Establish a regular QI process involving cross-functional teams	▪ Set aside regular meeting time for cross-functional QI team ▪ Select a QI methodology to structure improvement efforts ▪ Train team members on QI methodology ▪ Practice good meeting skills ▪ Regularly review data on ABCS outcome and process measures to understand areas for improvement ▪ Invite patient(s) to participate on the QI team
Identify at-risk patients for prevention outreach	▪ Understand current patient panel relative to ABCS ▪ Select actionable improvement goals based on ABCS data ▪ Recall patients overdue for care/outreach related to ABCS testing, education, counseling
Define roles and responsibilities (tasks) across the care team to identify and manage ABCS population	▪ Use workflow mapping to examine current processes and explore other approaches ▪ Introduce preventive screenings and educational materials for ABCS measures into workflow ▪ Develop/enable point of care reminders based on ABCS guidelines ▪ Scrub charts daily to flag patients needing support on ABCS
Deepen patient self-management support for action planning around ABCS	▪ Train staff in motivational interviewing ▪ Develop shared care plans with patients, emphasizing goal setting led by patient values ▪ Follow up with patient progress toward care plan goals
Develop robust linkage to smoking cessation, self-management programs, and other evidence-based community resources	▪ Create list of community resources and keep in a location accessible to all staff members ▪ Outreach to community resources to build referral pathway ▪ Provide list of resources to patients ▪ Proactively refer patients to community resources and assist in establishing patient with the resource

*ABCS* aspirin, blood pressure, cholesterol, smoking, *EMR* electronic medical record, *QI* quality improvement

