### Randomization and data analysis

#### Randomization

We are using a stratified randomization with enrolled practices categorized into one of six strata defined by PF support organization (Qualis Health or ORPRN), prior practice experience obtaining customized data to drive improvement (yes, no), and prioritization of the work by the practice (high, low). Information on the latter two variables is collected in the baseline practice survey prior to randomization. Within each stratum, practices are randomly assigned by a computer-generated randomization scheme to one of the four intervention arms developed by the biostatistician. The evaluation/analysis team [[name]] are blinded to assignment.

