**Fig. 2 Fig2:**
[figure not shown]
Project timeline and data collection windows

For the primary analysis to assess differences between the four intervention groups on the primary outcome practice-level proportion with blood pressure control at 1-year follow-up (blood pressure CQM), we will fit the following linear regression model:$$ {Y}_i={\beta}_0+{\beta}_1{X}_{1i}+{\beta}_2{X}_{2i}+{\beta}_3{X}_{3i}+{\beta}_{\mathrm{base}}{Y}_i^0+{\boldsymbol{\beta}}_z{\boldsymbol{Z}}_{\boldsymbol{i}}+{e}_i\ {e}_i\sim N\left(0,{\sigma}^2\right)\ i=1,\dots, N $$where *Y*
_*i*_ is clinics *i* blood pressure CQM at 1-year follow-up, *X*
_1*i*_, *X*
_2*i*_, and, *X*
_3*i*_ are three indicator variables for intervention assignment for site visit, educational outreach, or both, respectively, *Y*
_*i*_^0^ is baseline blood pressure CQM, and ***Z***
_***i***_ is a vector of other baseline covariates to adjust for differences between clinics including PF support organization (Qualis Health or ORPRN), baseline prior practice experience obtaining customized data to drive improvement (yes, no), and baseline prioritization of the work by the practice (high, low). We will use the Fisher’s protected least significant difference approach to control for multiple comparisons due to the comparison of four intervention arms. Specifically, we will first calculate an Omnibus *F* test to assess if there are any significant differences between intervention groups and only calculate pairwise comparisons if this omnibus test is statistically significant.

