A secondary aim of this study is to assess if PF alone improves clinic-level ABCS outcomes (note that PF is given to all practices in our randomized trial population). To address this aim, we will conduct an observational study using data from our randomized study practices and control practices from the DARTNet Institute. Specifically, we will have data on practice-level ABCS outcomes 1-year prior to PF roll-out in each of our randomized trial practices and 1-year post PF roll-out. To control for potential confounding, we will match each randomized control trial practice to one or more control practices matching on practice size (clinician FTE), QI measure reporting capabilities as measures by their ability to generate a custom report without support from their EHR vendor, and rural/urban location. For each matched pair, we will use the same data ascertainment windows based on when the randomized control trial practice had PF rolled out. This will control for temporal changes. We will conduct similar analyses as proposed for the randomized trial except that now outcome time is tied to PF roll-out, and we will only include a single intervention indicator that had or did not have PF.

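### The PF-versus-control analysis treats PF practices as independent although they share roughly 13–25 facilitators; any positive correlation within facilitator makes its standard error too small

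*Protocol article*

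**What the plan says.** **Delivery of PF.** Under Practice facilitation and support, geographic clusters of 10–20 "practices are assigned to each practice facilitator". Under Practice support interventions: "PF support is provided to all sites upon enrollment in the study for 15 months as a unifying approach". The target in Study setting and recruitment is 250 practices.

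**Randomisation.** Individual practices are allocated within strata: "Within each stratum, practices are randomly assigned by a computer-generated randomization scheme to one of the four intervention arms". The strata use the support organisation, not the facilitator, so one facilitator's practices can fall in any arm.

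**Primary model.** Under Data analysis, "we will fit the following linear regression model" introduces a regression with one independent normal residual per practice. The adjustment vector holds "other baseline covariates to adjust for differences between clinics including PF support organization (Qualis Health or ORPRN"), together with prior data experience and prioritisation. There is no facilitator term.

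**Secondary aim.** The last paragraph of Data analysis compares trial practices with matched external controls. It says the analysis will be like that of the randomised trial and names two changes: outcome time is tied to PF roll-out, and "we will only include a single intervention indicator that had or did not have PF". The controls, described under Study design, are a national sample of practices outside the study.

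**The concern.** The two comparisons differ in structure. Between the randomised arms, facilitators cross the arms, so whatever a facilitator adds is shared by all of them. Between PF practices and controls, every PF practice has a study facilitator and no control has one. Shared facilitator skill and shared locality then add variance to the PF mean that does not cancel, and a model with independent errors leaves it out.

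The listed covariates do not repair this. Support organisation has only two levels and is not defined for controls. Matching on practice size, reporting capability and rural or urban location does not address correlation among practices that share a facilitator.

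At stake is the secondary hypothesis. Because all four arms receive PF, this is the only planned comparison that bears on whether PF itself improves outcomes. Its confidence interval would be too narrow and its false-positive rate above the nominal level.

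**Working it through.** **1. The plan's own figure.** The article states power only for the randomised comparison. With 250 practices and 20% attrition, 200 remain, or 50 per arm. The residual SD is 0.26 × √(1 − 0.60²) = 0.208. A four-group F test (3 and 196 df, alpha assumed 0.05) with one arm, or all three enhanced arms, differing from the rest by 0.114 has power 80.6%. With 45 per arm and 0.121 it is 81.1%. The stated 80% reproduces. No power or precision figure is given for the PF-versus-control comparison.

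**2. Number of facilitators.** 250 / 20 = 12.5 and 250 / 10 = 25, so roughly 13–25.

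**3. Randomised arms.** Simulating the omnibus F test (4,000 trials per setting, 200 practices, 10–20 per facilitator, ICC 0 to 0.10) with a facilitator effect common to all arms, but ignored in the model, gave type I error of 4.3%–5.1%. There is no inflation.

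**4. PF versus control.** With *m* practices per facilitator and *k* controls per PF practice, equal variances and no within-pair correlation:

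- design effect on the PF side only: DEFF = 1 + (m − 1) × ICC
- true SE / model SE: R = √[(DEFF + 1/k) / (1 + 1/k)]
- actual two-sided error at nominal 5%: 2 × [1 − Φ(1.96 / R)]

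The documents give no ICC, so a range is assumed. For m = 15:

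| ICC | DEFF | Effective PF practices (200 / DEFF) | R, k = 1 | Type I error, k = 1 | R, k = 3 | Type I error, k = 3 |
|---|---|---|---|---|---|---|
| 0.02 | 1.28 | 156 | 1.068 | 6.6% | 1.100 | 7.5% |
| 0.05 | 1.70 | 118 | 1.162 | 9.2% | 1.235 | 11.2% |
| 0.10 | 2.40 | 83 | 1.304 | 13.3% | 1.432 | 17.1% |

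Example, ICC 0.05 and k = 1: R = √[(1.70 + 1) / 2] = √1.35 = 1.162; 1.96 / 1.162 = 1.687; error = 9.2%. The model's SE is then 1 − 1/1.162 = 14% too small.

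At 1:1 matching, for m = 10 and m = 20 the error is 6.0% and 7.2% (ICC 0.02), 7.7% and 10.7% (ICC 0.05), and 10.4% and 16.0% (ICC 0.10). If 20% attrition shrinks clusters evenly to 8–16 practices, ICC 0.05 gives 7.1%–9.5%.

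**5. Simulation check.** At 1:1 over 10–20 practices per facilitator, simulated error was 6.2%–7.4%, 7.8%–10.5% and 10.5%–15.8% at ICC 0.02, 0.05 and 0.10, and about 5% at ICC 0. The formula and the simulation agree to within about 1.3 percentage points.

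**6. Effect of ignored pairing.** If matched pairs have residual correlation *r* and the model ignores it, then at k = 1 R² = (DEFF + 1 − 2r) / 2. Assuming r = 0.10 and m = 15:

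- ICC 0.02: R² = (1.28 + 0.8) / 2 = 1.04, error 5.5%
- ICC 0.05: R² = (1.70 + 0.8) / 2 = 1.25, error 8.0%
- ICC 0.10: R² = (2.40 + 0.8) / 2 = 1.60, error 12.1%

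The two effects cancel when r = (DEFF − 1) / 2, that is at r = 0.14, 0.35 and 0.70 respectively.

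**The case against.** **The error structure is inferred.** The article writes no residual term for the matched comparison, and variance estimation for a secondary analysis is often left to an analysis plan. This has some force. But the article does say what the analysis is: the trial model with two named changes, neither of which concerns clustering. As stated, the model leaves facilitators out.

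**The size rests on an assumed ICC.** This stands. The relevant ICC is the residual one after adjustment for the baseline measure, which would absorb stable regional differences. At 0.02 or below the inflation is modest, and nothing in the article supports 0.10 in particular.

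**Matching works the other way.** This also stands. Positive within-pair correlation that the model ignores offsets part of the understatement, and at ICC 0.02 a pair correlation of 0.14 would remove it.

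**The target of inference is not stated.** If the question is only what this programme achieved with these facilitators, their average skill belongs to the effect and is not sampling error. Under a strict null of no PF effect, facilitator skill contributes nothing and only shared locality could inflate the error. The criticism therefore applies when the result is meant to inform PF more widely, which the article's Discussion indicates by pointing to future large-scale initiatives.

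**Two stronger readings to avoid.** A reader might infer that facilitator clustering also undermines the primary four-arm comparison and its power. The documents do not support this: practices are randomised individually across facilitators, and a common facilitator effect leaves the error rate near 5%. Nor may one conclude that the four-arm analysis is safe from every form of clustering. If enhanced-support effects varied by facilitator, simulated omnibus error was 5.8%–9.3% for assumed interaction variance shares of 0.02–0.05. The article gives no sign of how large such variation is, and no claim is made about it, or about clustering by exemplar host or academic expert.

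**Conclusion.** The point holds for the secondary PF-versus-control analysis. Facilitators are nested on the PF side only, and the stated independent-error model omits them. Any positive residual facilitator or locality correlation makes the standard error of the PF effect too small when inference extends beyond these facilitators.

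The size is conditional. With 15 practices per facilitator, 1:1 matching and no within-pair correlation, type I error is about 6.6%, 9.2% or 13.3% at ICC 0.02, 0.05 or 0.10. It is higher with more controls per practice and lower if pairs are positively correlated and the pairing is ignored. None of these ICCs comes from the documents, so the figures show sensitivity and do not estimate the actual error rate.

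The analysis is secondary and observational, and confounding threatens it as well; that is no reason to accept an interval that is too narrow. The primary outcome, the randomised comparison and the power statement are not called into question here.

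**What to change.** In the PF-versus-control analysis, specify one of the following:

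- a partially nested mixed model, with a facilitator random effect for PF practices only and a small-sample degrees-of-freedom correction; or
- cluster-robust standard errors by facilitator, each control practice being its own cluster, with a small-sample correction because there are only about 13–25 facilitators.

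In either case, account for the matched sets, state whether inference is to these facilitators or to PF more generally, and report the estimated ICC.

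The cost is analysis wording and a wider interval for the secondary aim. Under the 1:1 assumptions above, the standard error grows by a factor of about 1.07, 1.16 or 1.30 at ICC 0.02, 0.05 or 0.10, before the small-sample correction. No new data should be needed, since each practice is assigned to a facilitator. This point asks for no change to the four-arm model on account of a facilitator effect common to all arms.
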